### Blinding

This trial will be double-blind, hence, participants and study assessors will remain blinded to group assignment until after the follow-up visit (V3; last participant, last visit). Efficacy of blinding from the participants’ perspective will be determined by asking each participant at post-intervention visit (V2) and follow-up visit (V3) to provide guesses of the assigned intervention condition.

## Methods: data collection, management, and analysis

### Data collection methods

Medical, neuropsychological, behavioral, and physiological data will be collected from each participant. Details on data collection procedures are provided below; time points of collection are detailed in Table 1. To ensure the standardization of data collection, all study assessors will undergo systematic training. Most data will first be recorded on paper (see Table 1) and will be entered into electronic records after each study visit with quality checks ongoing throughout the study. Quality control will be ensured through regular data monitoring.

#### Medical history and examination

Medical history assessment will include information on demographics, past and current medication intake, and family history. Subsequently, medical and neurological examinations will be conducted, including measurements of systolic and diastolic blood pressure and heart rate at rest. In addition, venous blood samples will be taken. In order to additionally test the influence of spermidine intervention on age-related sarcopenia, muscle function and muscle strength will be assessed (only of participants consented for the muscle biopsy).

#### Neuropsychological and behavioral batteries

The trial will include validated paper-and-pencil and computer-based neuropsychological tests as well as behavioral questionnaires (see Table 1). These instruments were selected based on their sensitivity and relevance in the study of aging and in correspondence with protocols of ongoing studies [59–61]. The neuropsychological test battery will include tests on learning and memory, executive functions, attention and working memory, as well as sensorimotor speed. The questionnaire battery will comprise measures of psycho-affective characteristics, lifestyle information (dietary habits, cognitive attainment, and physical activity), quality of life, and personality traits.

With regard to the nature of the trial, several questionnaires will be applied to collect nutritional information from each participant. Specifically, these measures will include the Food Frequency Questionnaire (FFQ), the Mediterranean Diet Adherence Screener (MEDAS), and a diet questionnaire that was previously adapted from a qualitative food frequency list (FFL) used in several German large-scale surveys [19, 62] (see Table 1). Validity and reproducibility of the FFQ are well established and based on the gold standard by Willett and colleagues [63]. The FFQ was recently applied in the study of Eisenberg and colleagues [33], indicating that this questionnaire provides meaningful estimations about the participant’s polyamine intake per day.

Questionnaires will be completed on-site and at home by each participant. Trained raters will evaluate neuropsychological tests and questionnaires in accordance with existing guidelines in test or questionnaire manuals. If available, German versions of questionnaires are included. Otherwise, German translations will be acquired or provided by the DELCODE study [59].

#### Blood sampling, genotyping, and pre-analytics

Fasting venous blood samples will be collected to analyze various blood parameters and to conduct genotyping. Labor Berlin Charité Vivantes GmbH will perform analyses of blood samples for safety parameters and research parameters, including glucose metabolism and lipid profile, in accordance with established SOPs. Polyamine levels (spermidine, spermine, and putrescine), metabolomics, proinflammatory biomarkers, and neurotrophin levels in whole blood, serum and plasma samples will be analyzed by the Institute of Molecular Biosciences, University of Graz, Austria. In addition, analysis of intracellular proteins with focus on nutrient signaling, metabolic regulation, and membrane-bound cellular markers of aging will be measured in peripheral blood mononuclear cells (PBMCs) extracted from whole blood [64]. In isolated leukocytes obtained from blood samples, acetylation levels and autophagy flux will be analyzed in collaboration with the INSERM U1138, Centre de Recherche des Cordeliers, Paris, France. Genetic analyses will be conducted by the Department of Psychiatry, Martin Luther University, Halle-Wittenberg, Germany.

Preprocessing and intermediate storage of blood samples will be performed at the Charité NeuroCure – Labs and at the NeuroCure Clinical Research Center, Charité – Universitätsmedizin Berlin. Blood samples for Labor Berlin Charité Vivantes GmbH will be shipped immediately. All other samples will be stored at − 80 °C or at 4 °C in phosphate-buffered saline and sodium azide until shipment for further processing and analyses. NeuroHub biomarker management platform and LabVantage software will guarantee standardized workflows, documentation, and monitoring of pre-analytics including processing as well as storage as described previously [36, 65].

#### Magnetic resonance imaging

The MRI examination will take place on a 3-T scanner (Tim Trio, Siemens, Erlangen, Germany) at the *Berlin* Center for Advanced Neuroimaging (*BCAN*, Charité – Universitätsmedizin Berlin)*.* The SmartAge MRI protocol will include structural and functional sequences (see Table 2). For structural imaging, a T1-weighted three-dimensional magnetization-prepared rapid acquisition gradient echo (MPRAGE) sequence, a Fluid Attenuated Inversion Recovery (FLAIR) sequence, Diffusion Tensor Imaging (DTI), and a high-resolution T2-weighted structural scan will be acquired perpendicular to the longitudinal axis of the hippocampus. The protocol will further include the following functional sequences: a blood-oxygen-level-dependent (BOLD) functional echo planar imaging (EPI), as assessed during rest (resting-state functional MRI) and during task (task-related functional MRI), and pseudo-continuous arterial spin labeling (pCASL) for cerebral blood flow (CBF) quantification during rest [66, 67].

**Table 2 Tab2:** Neuroimaging data acquisition parameters

Sequence	Main parameters [orientation, TR/TE/TI, FOV, slices, voxel size]
Structural sequences	
T1 MPRAGE	Sagittal, TR/TE/TI = 1900/2.52/900 ms, 256 × 256 mm^2^, 192 slices, 1.0 × 1.0 × 1.0 mm^3^
FLAIR	Axial, TR/TE = 11,000/97 ms, 230 × 230 mm^2^, 50 slices, 1.2 × 1.2 × 2.5 mm^3^
DTI	Axial, TR/TE = 7500/86 ms, 220 × 220 mm^2^, 61 slices, 2.3 × 2.3 × 2.3 mm^3^, 64 directions (*b* = 1000)
High-resolution hippocampus TSE	Coronar, TR/TE = 8020/48 ms, 150 × 150mm^2^, 24 slices, 0.4 × 0.4 × 2.0 mm^3^
Functional sequences	
Resting-state fMRI	Axial, TR/TE = 2300/30 ms, 192 × 192 mm^2^, 34 slices, 3.0 × 3.0 × 4.0 mm^3^
Task-related fMRI	Axial, TR/TE = 2000/30 ms, 192 × 192 mm^2^, 32 slices, 3.0 × 3.0 × 3.0 mm^3^
pCASL	Axial, TR/TE = 4300/19 ms, 192 × 192 mm^2^, 22 slices, 3.0 × 3.0 × 5.0 mm^3^, LD/PLD = 1.5/1.5 s

*Abbreviations*: *DTI* diffusion tensor imaging, *FLAIR* fluid-attenuated inversion recovery, *fMRI* functional magnetic resonance imaging, *FOV* field of view, *LD* labeling duration, *MPRAGE* magnetization-prepared rapid acquisition gradient echo, *pCASL* pseudo-continuous arterial spin labeling, *PLD* post-label delay, *TE* echo time, *TI* inversion time, *TR* repetition time, *TSE* turbo spin echo

Functional MRI will include an associative face-name memory task, adapted and modified from a previous publication [68]. During the scanning session, the participants will learn 24 face-name pairs (encoding phase), which have to be correctly identified in a subsequent recognition phase. For details on this memory task, please refer to Sperling and colleagues [69, 70].

All MRI scans will undergo quality checks and will be evaluated quantitatively using state-of-the-art brain MRI software packages and toolboxes implemented in Statistical Parametric Mapping (SPM, Wellcome Department of Imaging Neuroscience), FSL (FMRIB Software Library, Oxford, UK), and FreeSurfer (Martinos Center for Biomedical Imaging, Massachusetts General Hospital, Boston, USA). Structural MRI scans will be used to examine the integrity of cerebral gray and white matter tissues, including assessments of volume, thickness, microstructure, and high-resolution volumetric quantification of medial-temporal structures [71]. Functional scans will be analyzed to assess brain activation patterns during the associative memory task as well as CBF maps and functional connectivity at rest.

#### Muscle tissue biopsy and muscle function (optional consent)

Muscle tissue biopsy will be performed at the Clinical Research Unit, Berlin Institute of Health (BIH, Charité – Universitätsmedizin Berlin). In total, 200–400 mg muscle tissue will be collected from the participant’s thigh (Musculus vastus lateralis). For this purpose, local anesthesia with lidocaine 1% without epinephrine will be administered. Subsequently, a skin incision (3–4 mm) will be made and the muscle tissue will be obtained by repeated needle biopsies (Bergström needle). Participants are asked to fast prior to the procedure for at least 8 h. After 12-month intervention time (V2) a second muscle tissue biopsy will be carried out at the same leg close to the first puncture site. Biopsy tissue processing will include snap freezing in liquid nitrogen and paraffin embedding. Samples will be stored at − 80 °C until analysis.

Potential changes in muscle autophagy markers in response to spermidine intervention will be quantified by immunohistochemical analysis of autophagic flux and autophagic capacity [72] as well as by acetylproteome analysis as an upstream regulator of autophagy [73].

In addition, non-invasive measurements of muscle function and muscle strength will be assessed during medical examination from all participants who consented to muscle biopsy, to determine age-related sarcopenia. For this purpose, the following standardized measurements of sarcopenia will be administered: Short Physical Performance Battery (SPPB) [74, 75], and a handgrip strength test [75]. The SPPB is a composite measure and will include 4-m gait speed, balance, and chair stand tests.

#### Positron emission tomography (optional consent)

Quantification of brain Aβ status is carried out using PET and the approved ligand FBB (Neuraceq™; Life Molecular Imaging (LMI)). The FBB PET images will be acquired using the PET/MR hybrid system (Siemens Biograph mMR) of the Institute of Diagnostic and Interventional Radiology and Nuclear Medicine, Charité – Universitätsmedizin Berlin. For data acquisition, 260–300 MBq of FBB PET tracer will be administered intravenously. Participants will undergo a static scan at 90–110 min after injection and images will be consistently reconstructed according to the current procedure guideline on brain PET imaging of the German Society of Nuclear Medicine [76].

The FBB PET scans will be processed using an automated pipeline based on the routines of the SPM software package, implemented in a MATLAB environment (Mathworks, Inc., Nattick, MA, USA). For each PET scan, intra-PET motion correction, construction of static standardized uptake value (SUV) images, and correction for partial volume effects using the Müller-Gärtner method [77] as implemented in the PETPVE12 toolbox [78] will be performed. Intensity scaling using the cerebellar cortex as reference region [79] will be applied to obtain standardized uptake value ratio (SUVr) images. Neocortical Aβ-plaques burden will be evaluated as the average FBB SUVr within a predefined composite of cortical regions-of-interest [76]. In addition, exploratory voxel-by-voxel analyses will be performed on the FBB SUVr images.

### Data management and monitoring

Documentation using a paper-based case report form (CRF) will be implemented. To certify excellent data quality, a good clinical practice (GCP) monitoring will be held on a regular basis. The SmartAge research team will be responsible for data management under the guidance of the principal investigator (AF). All CRF data will be entered into an electronic database with following quality control procedures: (a) double scoring and double entry of data points in the paper-based records and electronic records and (b) frequency distribution checks of outcome measures (not stratified by intervention group) to identify questionable data points.

### Adverse events monitoring and reporting

The occurrence of AEs and SAEs will be constantly monitored throughout the SmartAge trial. Participants will be instructed to immediately contact the research team in case of any self-noticed health changes or unexpected medical care visits. In addition, participants will receive a study pass, which informs about participation in the SmartAge trial and provides contact information in case of an SAE/hospitalization. All AEs and SAEs will be reported to and documented by the responsible study physician (SAEs within 24 h).

In general, the risk of health damage due to spermidine supplementation can be expected to be minimal, based on a prior interventional report [35] and our safety study [36]. Participants will be informed about all possible risks and can withdraw consent at any time without providing reasons. The expected “dropout” rate will be balanced in advance by the number of participants.

In case an SAE occurs, the study physician will first make an assessment as to whether or not a causal relationship with the intake of the investigational supplement is considered possible. Since this is a double-blinded trial, the assessment will be done without knowledge of group affiliation (spermidine and placebo). Emergency unblinding is possible, if the decision on follow-up medical treatment may depend on the participant’s allocated intervention during the trial. If more than three of the enrolled participants suffer from SAEs that are likely to be associated with spermidine intake (as assessed by the study physician), the SmartAge trial will be discontinued. All SAEs (whether or not related to the intervention) and all relevant pseudonymized documentation related to the SAE will be documented in the SAE report form, dated and signed by the principal investigator and included in the CRF documentation.

### Statistical methods

Statistical analyses of the primary outcome and secondary outcomes will be specified in the statistical analysis plan, to be written and registered before breaking the blind of study investigators. Statistical analyses of the primary outcome will be conducted by a designated statistician. Statistical analyses of secondary outcomes and additional exploratory analyses will be carried out by study investigators.

The primary outcome will be analyzed using an “intention to treat” (ITT) approach, consisting of all participants randomized into the trial, regardless of length of intervention. Subsequently, a “per protocol” analysis is carried out, including only those participants, who finished the 12-month intervention period. We will assess the between-group difference in the change of memory performance, operationalized by mnemonic discrimination performance, between baseline (V1) and the end of intervention (V2). Statistical analysis will be performed using an ANCOVA model with the change in memory performance (V2–V1) as dependent variable, intervention group as independent variable, and baseline memory performance as well as age as co-variates. Analyses of secondary endpoints will be conducted using comparable statistical methods. For example, analysis of change in memory performance between baseline (V1) and follow-up assessment (V3) will be carried out by means of ANCOVA. In this model, change in memory performance (V3–V1) will represent the dependent variable, with intervention group as the independent variable and baseline scores and age inserted as covariate.

In case of missing primary endpoints, the primary analysis will be done by using multiple imputation methods. It will further be investigated whether demographic or biological factors are associated with primary and secondary endpoints and / or modulate the response to the intervention, by integrating these variables into statistical models as covariates (or as interactive term with the intervention group). The main hypothesis is tested at a two-sided significance level of alpha = 0.05, using the ITT data set with multiple imputation.

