### Sample size

A power calculation was conducted to estimate the number of participants required to detect a group difference in the primary outcome (i.e., mnemonic discrimination performance) at the end of the intervention. Sample size estimation was based on behavioral data obtained in a phase IIa pilot trial [37]. In this pre-study on 30 SCD participants (dropout: *n* = 2) and a 3-month intervention period, we determined an effect size of Cohen’s *d* = 0.65 on the group difference in change of mnemonic discrimination performance between baseline (V1) and the end of intervention (V2). Since this is a first estimate of the effect size based on a small sample, we based our sample size estimation for the present phase IIb trial on a smaller effect size of Cohen’s *d* = 0.5. To demonstrate a significant effect in the primary outcome, 50 participants per group (including a 10% dropout rate) need to be incorporated in the analysis with an unpaired-sample *t* test (two-sided significance level = 0.05, power 80%). Sample size estimation was conducted using a conservative approach [57] based on an unpaired-sample *t* test, even though the intended analysis of the primary outcome will be performed using analysis of covariance (ANCOVA) models. Case number estimation was compiled with the R package “pwr” [58].

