## Methods: assignment of intervention

### Allocation

Participants will be randomly assigned to the spermidine or the placebo group. A blockwise (block size of 6) randomization sequence, stratified by age (60–70, 70–80, and 80–90 years) and sex, will be generated using a computer-based algorithm (http://www.randomization.com/). Participant allocation will be performed at a 1:1 ratio by a study investigator without involvement in outcome assessments.

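### Sex is a stratification factor but is missing from the stated primary and V3 ANCOVA models; if sex is prognostic, the standard error is slightly too large

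*Protocol article*

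**What the plan says.** Protocol article, Allocation: the sequence uses blocks of six and is "stratified by age (60–70, 70–80, and 80–90 years) and sex", which gives 3 × 2 = 6 strata. "Participant allocation will be performed at a 1:1 ratio". The abstract also names age and sex as the stratification factors.

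Protocol article, Statistical methods: the dependent variable of the primary ANCOVA is the V2–V1 change in memory performance, with "intervention group as independent variable, and baseline memory performance as well as age as co-variates". The model for the V3–V1 change again has "baseline scores and age inserted as covariate". Sex is in neither list. The other secondary endpoints are to be analysed by similar methods, with no covariates named.

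Sex does appear elsewhere. The same section allows demographic factors to enter further models as covariates or as interactions with group, and Outcome measures names sex among the moderators. The main hypothesis test is separate from these: it is the ANCOVA on the intention-to-treat set with multiple imputation. Full specification is deferred to an analysis plan, to be registered before unblinding.

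**The concern.** Blocking within sex makes the two arms nearly equal in their share of men and women. Any effect of sex on the outcome then largely cancels from the treatment comparison, so the true sampling variance of the estimate is smaller than under unstratified randomisation. A model without sex cannot take this into account: the variance due to sex stays in the residual, and the reported standard error is larger than the real one. The confidence interval is then wider than it need be, and the test is conservative.

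What is at stake is a little precision on the primary endpoint, which the design has already provided and the stated model does not use. Adding sex only after unblinding could look data-driven, so the choice is best fixed beforehand.

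**Working it through.** **Sample size used.** The article plans on "a smaller effect size of Cohen’s *d* = 0.5" ("two-sided significance level = 0.05, power 80" per cent) and states that "50 participants per group (including a 10% dropout rate) need to be incorporated in the analysis". Removing 10% dropout leaves 50 × 0.9 = 45 per group, so N = 90. The stated 50 does not itself reproduce: the exact two-sided t test needs 63.8, so 64 evaluable per group, and 64 / 0.9 = 71.1, so 72 with dropout. At 45 per group its power is 65%. That is a separate issue; here it only sets N and the level of power in the table.

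**Assumption.** Let R² be the share of the residual variance, after baseline and age, that sex explains. The article gives no value, so a range is shown. With equal numbers of men and women and residual SD 1, a given R² corresponds to a sex difference in change of 2√R² residual SDs.

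**Formula.** For balanced arms, SE without sex ≈ 2σ/√N = 2/√90 = 0.211 at σ = 1. With sex in the model, σ falls to √(1 − R²). The ratio of the two standard errors is about 1/√(1 − R²):
- R² = 0.02: 1/√0.98 = 1.010
- R² = 0.05: 1/√0.95 = 1.026
- R² = 0.10: 1/√0.90 = 1.054
- R² = 0.20: 1/√0.80 = 1.118

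**Simulation.** Permuted blocks of 6 within the 6 strata; 90 complete cases; sexes equally likely; age about normal (mean 69, SD 6, limited to 60–90) and entered as continuous; treatment effect 0.5 residual SDs; 5000 trials per setting. The two models were baseline + age and baseline + age + sex. Each cell gives the result without sex / with sex.

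| R² | Sex difference (SDs) | Mean model SE | Power | Rejection under the null |
|---|---|---|---|---|
| 0 | 0 | 0.2119 / 0.2120 | 64.9% / 64.8% | 4.7% / 4.7% |
| 0.01 | 0.20 | 0.2122 / 0.2112 | 65.1% / 65.6% | 5.6% / 5.7% |
| 0.02 | 0.28 | 0.2120 / 0.2099 | 64.0% / 64.9% | 4.8% / 5.1% |
| 0.05 | 0.45 | 0.2123 / 0.2070 | 64.4% / 65.9% | 4.2% / 4.8% |
| 0.10 | 0.63 | 0.2117 / 0.2008 | 63.8% / 67.7% | 4.4% / 5.3% |
| 0.20 | 0.89 | 0.2126 / 0.1900 | 66.1% / 74.6% | 2.9% / 4.5% |

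A run of 8000 trials per setting gave, at R² = 0.05, power 64.0% / 65.9% and null rejection 4.6% / 5.1%; at R² = 0.10, power 65.4% / 69.4% and null rejection 3.9% / 4.7%.

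**Reading the table.**
- The simulated standard errors have the ratios the formula predicts.
- The actual sampling SD of the estimate is nearly the same under both models (0.2058 / 0.2056 at R² = 0.05; 0.2030 / 0.2024 at R² = 0.10). Only the reported standard error differs, because the blocking has already done the balancing.
- The mean estimate was within 0.005 of the true value in every setting.
- Monte Carlo error on the null rejection rates is √(0.05 × 0.95/5000) = 0.003. Differences of half a point should not be over-read, and the 5.6% / 5.7% at R² = 0.01, which appears with and without sex, is within about two such errors of 5%.

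**The case against.** The strongest objection is that the size of the effect is unknown and may be zero. The baseline covariate already absorbs much of any sex difference in the level of MST performance. What matters is a sex difference in change at a given baseline and age, and the article neither reports nor implies one. This stands. A reader might infer that the treatment standard error is overstated as a matter of fact; the documents support only the conditional statement. An R² of 0.10 would also need a sex difference of 0.63 residual SDs, larger than the planned treatment effect of 0.5.

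Second, the direction is safe. The test remains valid, and at R² = 0.05 the conservatism in the type I error is hardly distinguishable from simulation noise. This also stands.

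Third, a reader might infer that sex is absent from the plan. It is not, given the moderator and covariate analyses. But those are additional analyses and leave the main test as stated. The unseen analysis plan may add sex; the article nevertheless writes out the covariate list for both models, and it is that list that does not match the randomisation.

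Fourth, a reader might infer that adding sex would cure the power shortfall. It would not: the shortfall comes from the sample size. The level of power shown is also model-dependent. The simulation puts d = 0.5 on the residual SD, whereas the article defines d on the change score and plans on a t test "even though the intended analysis of the primary outcome will be performed using analysis of covariance (ANCOVA) models", so power is higher if baseline and age explain variance. The complete-case simulation is a simplification too, since the primary analysis uses multiple imputation. The differences between the two models are more informative than the levels.

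**Conclusion.** The mismatch is real and stands in the text: randomisation is stratified by age and sex, while the primary and V3 models adjust for age and baseline only. Its consequence is conditional and modest. Over an assumed R² of 0.02 to 0.10, the standard error is about 1% to 5% too large and about 1 to 4 points of power are lost. At R² = 0 nothing visible changes; at R² = 0.20, shown only as an outer case, the excess is about 12%. There is no bias and no type I error inflation. This is a point of efficiency and consistency with the design and does not threaten the validity of the result. It is worth correcting because the gain may be useful and the cost is close to nil.

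**What to change.** In the analysis plan, before unblinding, write the primary model as change (V2–V1) = group + baseline MST + age + sex, and the V3 model as change (V3–V1) with the same terms. Carry sex into the comparable secondary ANCOVAs, each with its own baseline score, and into the multiple-imputation model. If there is a reason to leave sex out, state it.

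The cost is one degree of freedom: with 90 evaluable participants the residual degrees of freedom go from 90 − 4 = 86 to 90 − 5 = 85. No extra data are needed, since sex is known for everyone at randomisation, and the randomisation itself is untouched. The planned moderator analysis of sex can stay as it is.
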